## Introduction

1

The incidence of chronic diseases is progressively increasing, along with the associated care burden for families, general practitioners, and the National Health System (1–3). Patients affected by chronic conditions are complex and require strong interaction between primary care and specialized centers to ensure proper management of all phases of the disease, such as diagnosis, clinical exacerbation handling, and the definition of an individualized therapeutic program (4). Specifically, chronic heart failure (CHF) is a complex syndrome involving multiple regulatory systems and is associated with high rates of rehospitalization and mortality (5). The complexity of this condition often necessitates frequent access to hospital facilities for multidisciplinary evaluations and diagnostic exams, thereby increasing both direct and indirect costs (lost workdays, travel, inappropriate hospitalizations) (6, 7). For patients with multiple chronic conditions, whose continuous therapies and follow-up visits aim to extend the number of years lived without severe disabilities, it is crucial to create a “territorial network” that facilitates dialogue between local health services and secondary/tertiary care centers (8). This would promote resources optimization and reduce hospital admissions or services. Furthermore, appropriate management during the intervals between outpatient visits is essential. In recent years, there has been a growing adoption of telemedicine solutions, which, through information and communication technologies (ICT), enable the delivery of healthcare services outside traditional healthcare settings, even when the healthcare provider and patient are in different locations (9, 10). Telemedicine is a valuable tool that supports the continuity of care between hospitals and communities, improves access to health services, and optimizes chronic disease management (11, 12). It also helps enhance home care and reduce unnecessary travel, especially for patients living in remote areas (13). ICT is used to facilitate the exchange of information between care partners and to promote patient empowerment by providing devices for self-monitoring of biomedical parameters, which can be remotely monitored by healthcare professionals to tailor the treatment plan (14). CHF, in particular, is characterized by alternating periods of stability and clinical worsening, but over the last three decades, management of this condition has significantly advanced, with pharmacological and device-based therapies (15, 16). Among these, implantable defibrillators, alone or combined with cardiac resynchronization therapy, are equipped with algorithms that monitor signs of congestion through thoracic impedance. Despite their effectiveness, these devices are invasive and require surgical implantation (17, 18). Given the high burden and complexity of CHF, there is an increasing need for complementary data beyond clinical history and physical examination, including telemonitoring and biochemical information (19). In recent years, the most innovative scenario has been represented by disease management supported by wearable and non-invasive medical devices capable of continuously collecting physiological parameters useful for remote monitoring. These technologies are available in different formats—wrist-worn devices, chest sensors, and non-invasive multiparametric monitors—each with specific advantages. Among them, the Empatica EmbracePlus (Empatica Inc.) is a CE-certified wristband capable of recording multiple signals such as blood oxygen saturation (SpO₂), heart rate (HR) and variability (HRV), electrodermal activity (EDA), sleep quality (actigraphy), respiratory rate (RR), temperature, and fatigue detection (20–22). The Movesense MD sensor (Suunto/Kaasa Health) is a CE-marked chest-worn device validated for ECG and motion tracking (23), while the Polar H10 chest strap (Polar Electro), although primarily designed for sports and fitness, provides accurate HR and HRV measurements that can be integrated into telemonitoring programs (24, 25). In addition, a non-invasive multiparametric device allows real-time monitoring of several metabolic and hemodynamic variables (e.g., glucose, hemoglobin, blood pressure, and oxygen saturation), expanding the range of information available for clinical decision-making (26). When integrated with telemedicine platforms, electronic health records, and advanced analytics, these devices enable continuous monitoring, early detection of decompensation, and timely therapeutic adjustments (e.g., diuretic dosage). This comprehensive and patient-centered approach has the potential to improve self-management, optimize healthcare resource utilization, and reduce CHF exacerbations and hospitalizations. However, despite technological progress, most previous telemonitoring studies in CHF have relied on single-parameter measurements, intermittent data collection, or rule-based alert systems (27–29), which limit their ability to detect subtle and individualized early signs of clinical deterioration. Moreover, only a few studies have integrated continuous multimodal wearable signals, and the application of advanced artificial intelligence to real-time physiologic data remains limited (30, 31). SMART-CARE aims to address this knowledge gap by combining high-resolution, multi-sensor wearable data with AI-driven predictive analytics capable of identifying trends, detecting early physiological deviations, and generating personalized alerts. This approach is designed to overcome the limitations of earlier telemonitoring interventions and support a more proactive and individualized model of CHF management.

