### Outcomes

2.4

Both groups will undergo assessments at baseline, 3 months, and 6 months, including evaluations of functional status, echocardiographic parameters, biochemical markers (e.g., BNP, NT-proBNP, renal function), and quality of life assessed using the Kansas City Cardiomyopathy Questionnaire (KCCQ) (36–39) (Table 2).

**Table 2 T2:** SMART-CARE outcome measures by timepoint.

Outcome type	Outcome measure	Domain	Baseline	3 months	6 months
Primary	Change in Hospital Admissions	Clinical Events			✔
Secondary	Change in Quality of Life (KCCQ Score)	Quality of Life	✔	✔	✔
Secondary	Adverse Effects of CHF Therapy	Safety			✔
Secondary	Change in BNP Levels	Biochemical	✔	✔	✔
Secondary	Change in NT-proBNP Levels	Biochemical	✔	✔	✔
Secondary	Change in Serum Creatinine	Biochemical	✔	✔	✔
Secondary	Change in eGFR	Biochemical	✔	✔	✔
Secondary	Change in Serum Sodium	Biochemical	✔	✔	✔
Secondary	Change in Serum Potassium	Biochemical	✔	✔	✔
Secondary	Change in Serum Chloride	Biochemical	✔	✔	✔
Secondary	Change in HRV	Functional (ECG)	✔	✔	✔
Secondary	Change in Respiratory Rate	Functional (ECG)	✔	✔	✔
Secondary	Change in LVEF	Echocardiographic	✔	✔	✔
Secondary	Change in E/A Ratio	Echocardiographic	✔	✔	✔
Secondary	Change in LV End-Diastolic Volume	Echocardiographic	✔	✔	✔
Secondary	Change in LV End-Systolic Volume	Echocardiographic	✔	✔	✔

CHF, chronic heart failure; KCCQ, Kansas City Cardiomyopathy Questionnaire; BNP, B-type Natriuretic Peptide; NT-proBNP, N-terminal pro-B-type Natriuretic Peptide; eGFR, estimated Glomerular Filtration Rate; HRV, Heart Rate Variability; ECG, Electrocardiogram; LVEF, Left Ventricular Ejection Fraction; E/A Ratio, Early to Late Ventricular Filling Velocity Ratio; LV, left ventricle.

The primary outcome of the SMART-CARE study is the relative reduction (≥20%) in hospital admissions, including emergency department visits and unplanned hospitalizations, over a six-month follow-up period in the intervention group compared to standard care (40). Hospitalization data will be collected prospectively and analysed for frequency, duration, and cause.

Secondary outcomes include:

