Quality of Life (QoL): Measured using KCCQ at baseline, 3 months, and 6 months.Biochemical parameters: BNP, NT-proBNP, serum creatinine, eGFR, and serum electrolyte levels (sodium, potassium, chloride) at 3 and 6 months.Functional parameters: Variations in HRV and RR derived from wearable sensor data.Echocardiographic measures: LVEF, Early to Late Ventricular Filling Velocity Ratio (E/A ratio), and left ventricular end-diastolic and end-systolic volumes, measured at 3 and 6 months.Adverse events: Incidence of therapy-related complications such as hypotension and bradyarrhythmias.These outcomes will provide a comprehensive evaluation of the impact of AI-driven remote monitoring clinical status, functional performance, biomarker trends, and patient-reported outcomes in individuals with CHF. The measurements collected by the minimally invasive devices will be uploaded to the “Smartcare” platform and analyzed using machine learning (ML) techniques to develop multiparametric scores capable of identifying the specific trajectory of patients affected by HF.

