#### Primary endpoint analysis

2.6.1

To assess the primary endpoint of the study, Kaplan–Meier survival curves will be constructed to compare the time to first hospitalization between groups. Group differences will be evaluated using the log-rank test. Subsequently, a Cox proportional hazards regression analysis model will be performed to examine the association between the variable “Device Use (Yes vs. No)” and the reduction in hospital admissions. The model will be adjusted for all statistically significant covariates identified through ANOVA between the two groups. To mitigate selection bias resulting from the non-randomized design, propensity score methods will be applied. The propensity score will be estimated using baseline variables including age, sex, LVEF phenotype, NYHA class, major comorbidities (hypertension, atrial fibrillation, diabetes mellitus, COPD/OSA, obesity), prior HF hospitalizations, baseline biomarkers (BNP/NT-proBNP, renal function, electrolytes), and key echocardiographic indices (LVEF, LV volumes). A 1:1 nearest-neighbour matching approach without replacement will be used. Covariate balance between groups will be evaluated using standardized mean differences (SMD), with values <0.10 indicating adequate balance. Results will be expressed as hazard ratios (HR) with corresponding 95% confidence intervals (CI).

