#### Handling of missing data and dropouts

2.6.4

Missing data and incomplete follow-up will be handled according to established recommendations for observational cohort studies. For clinical, biochemical, and echocardiographic variables, the pattern and mechanism of missingness will be evaluated. When data are missing at random (MAR), multiple imputation using chained equations (MICE) will be applied to reduce bias and preserve statistical power. In case of non-random missingness, sensitivity analyses will be performed using complete-case analysis and worst-case/best-case scenarios. For time-to-event analyses, dropouts will be treated as censored observations at the last available follow-up. Device adherence will be quantified as the percentage of monitoring days with valid wearable data; predefined thresholds for minimum acceptable adherence will be applied in sensitivity analyses. Per-protocol and intention-to-monitor analyses will be conducted to assess the robustness of the findings with respect to missing data and incomplete device use.

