## Limitations

5

This study has several potential limitations that should be acknowledged. First, the non-randomized design may introduce selection bias, although the use of statistical adjustment methods (including multivariable regression and propensity score analyses) is expected to mitigate this risk. Second, the adoption of wearable devices may be influenced by a digital divide, with older or less digitally literate patients potentially underrepresented in the intervention group, which could limit the generalizability of the findings. Third, the reliance on continuous biometric monitoring and AI-driven alert generation raises the possibility of false positives, which may result in unnecessary clinical evaluations and potentially increase healthcare utilization. Conversely, false negatives cannot be excluded, with the risk of delayed detection of clinical deterioration. Finally, adherence to wearable use may vary over time, and incomplete data capture could affect the robustness of the analyses.

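### Death is in no listed outcome and by implication is censored in the primary analysis, so the admission hazard ratio alone cannot show net benefit.

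*Protocol article*

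**What the plan says.** Section 2.4 (Outcomes) defines the primary outcome as a relative reduction of at least 20% in "hospital admissions, including emergency department visits and unplanned hospitalizations, over a six-month follow-up period in the intervention group compared to standard care". It adds that hospitalizations will be analysed for frequency, duration and cause. Table 2 has 16 rows, one primary and 15 secondary, and none is mortality. The only safety item in the text is "Adverse events: Incidence of therapy-related complications such as hypotension and bradyarrhythmias".

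Section 2.6.1 (Primary endpoint analysis) uses Kaplan-Meier curves and the log-rank test to "compare the time to first hospitalization between groups". A "Cox proportional hazards regression analysis model will be performed to examine the association" between device use and admissions, and results are expressed as HRs. No competing-risk method and no composite with death is named.

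Section 2.6.4 (Handling of missing data and dropouts) has one rule for the time-to-event analyses: "For time-to-event analyses, dropouts will be treated as censored observations at the last available follow-up". It does not mention death.

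Elsewhere, the Introduction says that chronic heart failure "is associated with high rates of rehospitalization and mortality". Section 5 (Limitations) says of the alert system: "Conversely, false negatives cannot be excluded, with the risk of delayed detection of clinical deterioration".

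**The concern.** When the event is hospitalization only, a patient who dies without having been admitted leaves the risk set without an event. In the planned curves and models that patient cannot be told apart from someone who withdrew. Yet death ends the possibility of admission and shares its causes.

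Three consequences follow:

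- One minus Kaplan-Meier estimates admission risk in a hypothetical population without deaths, so it overstates the proportion actually admitted.
- The gravest form of the failure conceded in Limitations, a missed deterioration that ends in death outside hospital, enters no listed outcome. The groups are formed by willingness to wear the device (section 2.2), so unequal mortality is plausible even if the device does nothing.
- A device that gets patients into hospital who would otherwise have died raises the admission hazard and looks less effective.

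At stake is a claim of clinical benefit resting on an admission HR that is silent about deaths in either direction.

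**Working it through.** **Inputs.** From the article: a 20% relative reduction, represented here by a true admission HR of 0.80; six months of follow-up; 300 patients. Not in the article, so assumed: control admission risk 20–40%; six-month death risk 2–10%; constant hazards; and, for the counts in step 2, 150 patients per group. Each risk is the one that would apply without the other event. The article gives no mortality figure to reproduce.

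**Formulas.** Cumulative hazards over six months are a = −ln(1 − admission risk) and d = −ln(1 − death risk), with subscripts C for control and D for device.
- Admission-or-death HR = (0.8a + d_D) / (a + d_C).
- Proportion actually admitted first = a/(a + d) × [1 − exp(−(a + d))], with 0.8a in place of a for the device group.

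**1. Unequal deaths, 2% control and 8% device, 30% admission risk.** Here a = 0.3567, d_C = 0.0202 and d_D = 0.0834. The death-censored admission HR stays at 0.80. The admission-or-death HR is (0.2853 + 0.0834) / (0.3567 + 0.0202) = 0.3687 / 0.3769 = 0.98. At 40% admission risk it is 0.93, and at 20% it is 1.08.

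**2. The same case as expected counts, 150 per group.**

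| | Control | Device |
|---|---|---|
| First event is admission | 0.2972 × 150 = 44.6 | 0.2386 × 150 = 35.8 |
| First event is death | 0.0168 × 150 = 2.5 | 0.0697 × 150 = 10.5 |
| Either | 47.1 | 46.3 |

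The planned analysis sees only the first row.

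**3. Other death splits at 30% admission risk.** With 5% in both groups, (0.2853 + 0.0513) / (0.3567 + 0.0513) = 0.83. With 5% control and 2% device, (0.2853 + 0.0202) / 0.4080 = 0.75.

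**4. Deaths turned into admissions.** If the device converts all pre-admission deaths (5%) into admissions, the admission HR becomes (0.2853 + 0.0513) / 0.3567 = 0.94 instead of 0.80. Over 2–5% deaths and 20–40% admission risk it runs from 0.84 to 1.03. This is the extreme case, because every such death is converted.

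**5. Lost time at risk alone, no admission effect.** With deaths of 2% and 8% at 30% admission risk, the proportions admitted are 0.2972 and 0.2885, a ratio of 0.97. Over the unequal death splits tried, this ratio ran from 0.97 to 1.03. A simulation in which admission and death share a gamma frailty of variance 1 gave censored HRs of 0.98 to 1.02.

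**6. Overstatement by one minus Kaplan-Meier.** It would show 30.0% when 29.7% are actually admitted (2% deaths), 28.9% (8%) or 28.6% (10%), which is 0.3 to 1.4 percentage points too high.

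**The case against.** The strongest reply is that the plan states no wrong rule. Section 2.6.4 speaks of dropouts and never says that a death is one. A full protocol or statistical analysis plan, not shown, may define how death is handled. NYHA class IV, planned transplant or assist device, severe renal impairment and terminal illness are excluded, and patients must be stable on optimized therapy, so deaths within six months may be few. The Introduction describes heart failure in general, not this cohort.

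Much of this stands. Censoring of deaths is inferred from the event definition and the methods named, and the size is unknown. It does not remove the point: the article sets out its outcome list and primary method in detail, and neither has a place for death. Table 1 also requires a hospitalization or an outpatient visit with intravenous therapy for heart failure in the past 12 months, so deaths cannot be assumed negligible.

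A reader might draw stronger conclusions that the document does not support:

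- *A patient who dies at home counts as never admitted.* In Kaplan-Meier, log-rank and Cox that patient is at risk until death and then leaves. The description fits only the analysis of admission frequency in section 2.4, where the patient contributes zero admissions.
- *The Cox HR is invalid.* With deaths censored it is the cause-specific HR for admission, which a competing-risk report would also give. What is missing is its companion for death.
- *As many deaths as the targeted difference in admissions would mean bias of that size.* Only deaths before any admission matter, and mainly their imbalance or their exchange with admissions. The 0.75–0.98 range in the working belongs to a different endpoint and is not error in the admission HR.
- *Values after death will be imputed as missing at random.* Section 2.6.4 evaluates the mechanism first and limits multiple imputation to data missing at random. It simply has no rule for values after death.

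**Conclusion.** The concern holds as a gap in what the primary result can show. Death is in no outcome, and the primary analysis has no way to represent it other than censoring. The admission HR remains interpretable as a cause-specific quantity, but it cannot support a claim of net benefit alone.

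The size depends on mortality, which the document does not give. Under the assumed 30% admission risk and constant hazards, an admission HR of 0.80 is compatible with an admission-or-death HR of 0.75 to 0.98 across the death splits shown. The upper end needs a fourfold excess of deaths in the device group. If mortality is low and equal between groups, the practical effect is slight. Severity: should be fixed.

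**What to change.** 1. Ascertain vital status at six months for every patient, including dropouts, and add all-cause death by group to section 2.4 and Table 2.
2. State in sections 2.6.1 and 2.6.4 that death is a competing event and not a dropout.
3. Show Aalen-Johansen cumulative incidence of admission in place of Kaplan-Meier.
4. Label the Cox result a cause-specific HR for admission and report the HR for death beside it.
5. Add time to first admission, emergency visit or death as a supportive analysis, reported together with the primary result.
6. State that values after death are not imputed.

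The cost is small. All patients already have a six-month evaluation, so the extra work is one vital-status check for those who have dropped out, a few sentences in sections 2.4, 2.6.1 and 2.6.4, and a little more analysis. The primary outcome and the Cox model stay as they are.

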### Groups and interventions

2.2

Participants will be allocated to one of two non-randomized, parallel groups based on their acceptance to use the wearable device:
Intervention Group – AI-Based Remote Monitoring: Patients in this group will wear wearable devices continuously over a six-month period. The wearable device collects multimodal biometric data, including SpO₂, HRV, EDA, respiratory rate, skin temperature, pulse rate, and sleep metrics (actigraphy). These data are automatically transmitted to the SMART-CARE platform, where advanced AI algorithms analyse trends and detect early signs of clinical deterioration. In case of abnormal findings, the system generates alerts for the clinical team, which may initiate teleconsultations, therapy adjustments, or in-person evaluations to prevent acute decompensation.Control Group – Standard Clinical Follow-Up: Participants in the control group will receive standard CHF management in accordance with current European Society of Cardiology (ESC) guidelines. This includes outpatient visits every three months, ECG and echocardiographic assessments, and laboratory evaluations. No remote monitoring will be applied in this group. Clinical decisions, including medication adjustments, will be based on periodic clinical evaluations and patient-reported symptoms.

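### The adherence-threshold and per-protocol analyses can drop device patients because they were admitted, while no control can be dropped, so they can favour the device with no true effect

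*Protocol article*

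**What the plan says.** Section 2.6.4 of the protocol article defines the measure: "Device adherence will be quantified as the percentage of monitoring days with valid wearable data". It then says that "predefined thresholds for minimum acceptable adherence will be applied in sensitivity analyses", and adds: "Per-protocol and intention-to-monitor analyses will be conducted to assess the robustness of the findings with respect to missing data and incomplete device use". It gives no threshold value. It does not say whether in-hospital days count as monitoring days, whether counting stops at an event, or who belongs to the per-protocol set.

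Section 2.2 sets the wear period for the intervention group: "Patients in this group will wear wearable devices continuously over a six-month period". Of the control group it says: "No remote monitoring will be applied in this group".

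The primary analysis in Section 2.6.1 is to "compare the time to first hospitalization between groups", followed by a Cox model on device use. The propensity score there is built from baseline variables only. Section 2.4 defines the admissions outcome as "including emergency department visits and unplanned hospitalizations, over a six-month follow-up period".

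**The concern.** Adherence is measured after baseline, over the same months in which the outcome occurs, and the outcome can lower it. A patient in hospital may produce no valid wearable data and may be slower to resume wear, or never resume. If such a patient then falls below the minimum, the analysis loses a device patient with an event. A control with the same admission stays in, because no wear criterion can apply to someone without a device. Events are then removed from one group only.

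Baseline propensity scores do not repair this, since the selection acts through something that happens after baseline and partly because of the event.

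What is at stake is how the robustness analyses are read. They are offered as checks on incomplete device use. A null intention-to-monitor result beside a favourable result in adherent patients would suggest that the device works when worn, when the gap could come from the selection rule alone.

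**Working it through.** **The plan's own figures.** The document gives no figure for adherence, its threshold or the resulting bias, so there is nothing to reproduce. The only yardstick is the 20% relative reduction targeted in Sections 2.4 and 2.6.3.

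**Inputs from the document.** Six months of wear (taken as 182 days); 300 patients; time to first event with a Cox model; two-sided 5% level; no device in controls.

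**Assumptions not in the document.** 150 per group; six-month admission risk of 30% or 50%; mean stay 8 days without valid data; thresholds of 50%, 70% and 80%; personal daily wear probability w from a Beta(8,2) distribution (mean 0.80), independent of risk; several patterns of wear after discharge.

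**Step 1: what one admission does to adherence over 182 days.**
- Wear resumes after 8 days: expected adherence = w × (182 − 8)/182 = 0.956w. The loss is at most 8/182 = 4.4 points. To pass 70% the patient needs w ≥ 0.70/0.956 = 0.73; to pass 80%, w ≥ 0.80/0.956 = 0.84.
- A further 14-day pause after discharge: w × (182 − 22)/182 = 0.879w. To pass 70% needs w ≥ 0.80; to pass 80%, w ≥ 0.91.
- Wear stops for good at an admission on day 91: w × 91/182 = 0.50w, below every threshold considered for any w under 1.

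A patient with no admission needs only w of about 0.70 or 0.80. The bar is higher for admitted device patients.

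**Step 2: effect on the comparison when the true hazard ratio is 1.** Device patients below the threshold are removed, all controls are kept, and an unadjusted Cox model is fitted (4000 simulated trials per scenario). Ranges cover the 30% and 50% risks.

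| After admission | 50% threshold | 70% | 80% |
|---|---|---|---|
| Hospital days count as missed, wear resumes | 0.99–1.00 | 0.93–0.94 | 0.82–0.85 |
| Same, 14-day pause after discharge | 0.97–0.98 | 0.76–0.79 | 0.42–0.46 |
| Same, 25% stop for good | 0.84–0.85 | 0.76–0.78 | 0.65–0.69 |

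Two-sided rejection across the thresholds is 4.5% to 11% in the first row and 12% to 36% in the third. A separate null simulation gave 0.93 to 0.95 at 70% and 0.81 to 0.85 at 80% with wear resuming, and about 0.80 at 70% if 20% stop.

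**Step 3: hand check of one cell.** At 30% risk, an 80% threshold and wear resuming, 25.6% of the retained device patients have an event against 30.0% of controls. With exponential times the hazard ratio is about ln(1 − 0.256)/ln(1 − 0.300) = 0.296/0.357 = 0.83, in line with the simulated 0.82.

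**Step 4: when the bias goes away.**
- No selection on adherence: hazard ratio 1.00, rejection 4.9% to 5.2%.
- In-hospital days left out of the denominator and wear resumes: 1.00, rejection 4.6% to 5.3%.
- In-hospital days left out but 25% stop: 0.79 to 0.85, rejection 11% to 16%. Excluding hospital days alone is therefore not enough.
- Adherence counted only up to first admission or censoring: 0.99 to 1.02, rejection 4.4% to 5.4%, at every threshold and risk tried.

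**The case against.** The strongest reply is that the text does not contain the rule being criticised. The thresholds belong to sensitivity analyses, the per-protocol analysis stands in its own sentence, and its population is open. The denominator is not stated to be the whole six months. The thresholds are called predefined, which suggests that a fuller plan, not shown here, holds the details. An article may leave the threshold value and the set definition to that plan.

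This stands in part. A reader might infer that the per-protocol set is chosen by whole-period adherence. That is a natural reading of an analysis aimed at incomplete device use, but the document does not say it, and the missing definition is not itself the fault. The point concerns the measure that the article does state, to which thresholds are expressly applied: nothing in its wording keeps post-event days out.

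The second reply is that the bias may be small. That also stands. One 8-day stay costs at most 4.4 points, and with a low threshold and wear resuming almost nothing happens. Lasting loss of wear after admission is an assumption, and Section 2.5 describes continuous technical and clinical support that could limit it. Emergency visits without a stay count towards the outcome but may cost little or no wear time, so charging every event 8 days overstates the effect for those.

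Third, Section 5 already warns that adherence may vary and affect robustness. It does not recognise that an admission can itself lower adherence, which is what gives the bias its direction.

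**Conclusion.** As written, the adherence measure allows outcome-dependent removal of patients from the device group only, in the threshold sensitivity analyses and, if defined in the same way, in the per-protocol analysis. Under no true effect the direction favours the device. The size runs from nil (50% threshold, wear resumes) through a hazard ratio of 0.93 to 0.95 (70%, wear resumes) to about 0.80 (70%, a fifth stop) and 0.81 to 0.85 (80%, wear resumes). The last two are close to the 20% reduction the study seeks. All of this rests on the assumed risk, stay, wear distribution, threshold and stopping share. The simulations are unadjusted and omit the matching.

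Two stronger readings are not supported. One is that these analyses are bound to show a spurious benefit: they need not, as the scenarios with no bias show. The other is that the main result is biased: Section 2.6.1 compares groups by device use with no stated adherence restriction, and an intention-to-monitor analysis is planned. The matter deserves correction because the exposed analyses are offered as evidence of robustness.

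**What to change.** In Section 2.6.4:
- For the threshold and per-protocol analyses, compute adherence only over days before the first primary event or censoring. Alternatively, use adherence in an early landmark window (for example the first 30 days), with both groups restricted to patients event-free at the landmark and followed from there.
- Re-estimate the propensity score and repeat the matching after low adherers are removed, so that the remaining device patients are compared with similar controls.
- State that intention-to-monitor is the primary analysis set and that the adherence-based analyses are supportive.

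The cost is a few sentences and some extra programming, with no new data. A landmark analysis loses the events inside its window. Neither version removes every difference between adherent and non-adherent patients: wear may fall as a patient worsens before an event, and adherent patients may differ in ways the baseline variables miss. The simulations assumed wear independent of risk, so they do not cover this.
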